# An Exercise Intervention to Unravel the Mechanisms Underlying Insulin Resistance in a Cohort of Black South African Women: Protocol for a Randomized Controlled Trial and Baseline Characteristics of Participants

**DOI:** 10.2196/resprot.9098

**Published:** 2018-04-18

**Keywords:** diabetes mellitus, type 2, insulin resistance, body fat distribution, adipose tissue, skeletal muscle, gastrointestinal microbiome, exercise, fatty liver, inflammation, energy metabolism, cardiorespiratory fitness, lipids, metabolomics, fatty acids, diet records, mitochondria, ectopic fat

## Abstract

**Background:**

The pathogenesis of type 2 diabetes (T2D) in black African women is complex and differs from that in their white counterparts. However, earlier studies have been cross-sectional and provide little insight into the causal pathways. Exercise training is consistently used as a model to examine the mechanisms underlying insulin resistance and risk for T2D.

**Objective:**

The objective of the study was to examine the mechanisms underlying the changes in insulin sensitivity and secretion in response to a 12-week exercise intervention in obese black South African (SA) women.

**Methods:**

A total of 45 obese (body mass index, BMI: 30-40 kg/m^2^) black SA women were randomized into a control (n=22) or experimental (exercise; n=23) group. The exercise group completed 12 weeks of supervised combined aerobic and resistance training (40-60 min, 4 days/week), while the control group maintained their typical physical activity patterns, and both groups were requested not to change their dietary patterns. Before and following the 12-week intervention period, insulin sensitivity and secretion (frequently sampled intravenous glucose tolerance test) and its primary and secondary determinants were measured. Dietary intake, sleep quality and quantity, physical activity, and sedentary behaviors were measured every 4 weeks.

**Results:**

The final sample included 20 exercise and 15 control participants. Baseline sociodemographics, cardiorespiratory fitness, anthropometry, cardiometabolic risk factors, physical activity, and diet did not differ between the groups (*P*>.05).

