Exercise training, via its effects on multiple organs and systems, reduces insulin resistance and the risk of T2D (for reviews [20-22]). Recent studies have suggested an important crosstalk between skeletal muscle, liver, adipose tissue and the pancreas [23-25], which is altered in response to exercise training [23]. The effects of exercise training on insulin sensitivity are primarily through insulin action in skeletal muscle [26], which involves many mechanisms, including changes in the insulin signaling, inflammation, reactive oxygen species (ROS), metabolic flexibility, mitochondrial biogenesis, and ectopic fat accumulation. Within adipose tissue, exercise training decreases the obesity-induced dysregulated expression of adipokines, adipocyte size, ROS and inflammation, and increases vasculature [27]. In addition, the importance of the gastrointestinal microbiome for diabetes risk has recently been recognized [28] and is responsive to exercise [29,30]. Indeed, advances in omics technologies have improved our understanding of systems biology in diseased states and can be used to identify novel pathways underlying insulin resistance and T2D risk.

Although, we can identify biological and physiological correlates of insulin resistance in black women, these may merely reflect adaptations to environmental and lifestyle factors. There are marked ethnic differences in socioeconomic status, dietary intake, and physical activity between black and white SA women [12]. In terms of physical activity, black women accumulate activity through walking for transport (typically performed at a low intensity), while participation in leisure activities that are generally performed at moderate-to-high intensities is uncommon [12,31]. Accordingly, black women have very low cardiorespiratory fitness levels, which associates with their high levels of obesity and insulin resistance [32].

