## Results

### Participant Enrollment, Allocation, Follow-Up, and Analyses

Information on participant enrollment, allocation, follow-up, and analysis is shown in Figure 2. Standards of reporting were based on the CONSORT 2010 checklist for randomized control trials. A total of 45 participants were enrolled in the study and randomized into exercise (n=23) and control (n=22) groups. Of these, 10 participants did not complete the intervention (dropout; n=3 exercise, n=7 control) resulting in a final sample of 20 exercise and 15 control participants.

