### Participant Baseline Characteristics

The sociodemographic characteristics of the participants at baseline are presented in Table 1. The average age of the whole group (n=45) was 24 (SD 4) years. Sociodemographic characteristics were not different between participants of the exercise, control, and dropout groups. The majority (67%, 30/45) of participants had completed at least grade 12 education, and 27% (12/45) of participants were currently enrolled students, while 51% (23/45) were employed. A quarter of the participants earned less than R2500/month (US $210/month at exchange rate of R11.9/US $, 13 February 2018), whereas 42% (19/45) earned between R2500-R5000/month (US $210-420/month), and the remaining participants (31%, 14/45) earned greater than R5000/month (US $420/month). Most of the participants were not married (89%, 40/45) and 42% (23/45) had at least 1 child. Apart from hypertension (42%, 19/45) and diabetes (13.6%, 6/45), the known family history of disease was relatively low.

**Table 1 table1:** Baseline sociodemographic characteristics.

Variables		Control (n=15)	Exercise (n=20)	Dropout (n=10)	*P* value
Age in years, mean (SD)		24 (4)	23 (3)	26 (4)	.24
Informal housing, n (%)		6 (40)	4 (20)	6 (60)	.09
Housing density (persons/room), median (interquartile range)		1.3 (1.0-1.6)	1.0 (0.8-1.5)	1.0 (1.0-2.7)	.38
Asset index (% of 14 commodities), n (%)		53 (15)	54 (20)	47 (23)	.62
**Education, n (%)**					.87
	< Grade 12	6 (43)	5 (25)	3 (30)	
	Grade 12	5 (36)	9 (45)	4 (40)	
	Tertiary	3 (21)	6 (30)	3 (30)	
**Employment, n (%)**					.63
	Employed	9 (60)	10 (50)	4 (40)	
	Student	5 (33)	9 (45)	4 (40)	
	Unemployed	1 (7)	1 (5)	2 (20)	
**Income, n (%)**					.09
	R0-2499/month	6 (40)	2 (10)	4 (40)	
	R2500-R4999/month	7 (47)	8 (40)	4 (40)	
	>R5000/month	2 (13)	10 (50)	2 (20)	
Marital status, married, n (%)		1 (7)	3 (15)	1 (10)	.73
**Parity, n (%)**					.33
	None	7 (48)	15 (75)	4 (40)	
	1 child	4 (27)	2 (10)	3 (30)	
	2-3 children	4 (27)	3 (15)	3 (30)	

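### The Abstract reports no baseline difference between the exercise and control groups, but the P values come from a three-column test with pooled dropouts, and the two analysed arms differ markedly on income

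*Protocol article*

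**What the plan says.** The Results paragraph of the Abstract states "The final sample included 20 exercise and 15 control participants". The next sentence reads "Baseline sociodemographics, cardiorespiratory fitness, anthropometry, cardiometabolic risk factors, physical activity, and diet did not differ between the groups" and attaches P>.05.

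The body text describes a different comparison. Under Participant Baseline Characteristics it says "Sociodemographic characteristics were not different between participants of the exercise, control, and dropout groups". Tables 1 to 3 carry three columns (control, exercise, dropout; 15, 20 and 10 women in Table 1) and one P value per variable. The section on enrollment and follow-up gives the make-up of the third column: "10 participants did not complete the intervention (dropout; n=3 exercise, n=7 control").

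The two lower income rows of Table 1, in the column order control, exercise, dropout, are "R0-2499/month 6 (40) 2 (10) 4 (40") and "R2500-R4999/month 7 (47) 8 (40) 4 (40"). The top band, above R5000 a month, is 2 (13%), 10 (50%) and 2 (20%). The printed P for income is .09. Table 3 gives mean height as 1.62, 1.57 and 1.60 m, each with SD .06, and P=.05.

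**The concern.** After a sentence that names two groups, a statement about the groups is read as exercise against control. That comparison is not reported anywhere. No column in the tables is a randomised arm: two are completers only, and the third pools women lost from both arms. An omnibus test over three columns can stay above .05 while two of the columns differ clearly, because the third adds degrees of freedom and may lie between the other two.

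The analysed sample consists of completers after unequal dropout (3/23 exercise, 7/22 control), so randomisation alone does not guarantee its comparability. The third objective correlates changes in insulin sensitivity and secretion with changes in determinants that include diet and physical activity, and randomisation does not protect such correlations from confounding. The Introduction says of biological correlates of insulin resistance that "these may merely reflect adaptations to environmental and lifestyle factors", and goes on to mention socioeconomic status. A reader told that sociodemographics are balanced has no prompt to consider income.

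**Working it through.** **Inputs.** Income counts (low, middle, top band) from Table 1: control 6, 7, 2; exercise 2, 8, 10; dropout 4, 4, 2. Height from Table 3: 1.62, 1.57 and 1.60 m, SD .06 each, n = 15, 20, 10. Dropout split from the enrollment section: 7 control, 3 exercise.

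**1. Reproduce the printed figures.**
- Income, Pearson chi-square on all three columns: 8.07, df = (3−1)(3−1) = 4, P=.089. Printed: .09. The same three-column test also returns the printed P for education (.87), employment (.63), parity (.33), marital status (.73) and informal housing (.09). The tabled values are therefore three-group tests.
- Height, one-way ANOVA from the rounded summaries: grand mean (15×1.62 + 20×1.57 + 10×1.60)/45 = 1.5933; between-group sum of squares .0220; F = (.0220/2)/.06² = 3.06 on 2 and 42 df, P=.058. The printed .05 lies within the range that rounding allows.

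**2. Compare the two analysed arms only.**
- Income: the expected counts are 3.43, 6.43, 5.14 (control) and 4.57, 8.57, 6.86 (exercise). Chi-square = 1.929 + .051 + 1.921 + 1.446 + .038 + 1.440 = 6.83, df 2, P=.033. The exact test gives about .04, and a rank test on the ordered bands .011.
- Top band: 10/20 = 50% against 2/15 = 13%, a gap of 37 percentage points; Fisher P=.034.
- Height: t = (1.62 − 1.57)/[.06 × √(1/15 + 1/20)] = .05/.0205 = 2.44, df 33, P=.020. Over all roundings that also reproduce a three-group P of .05, the two-arm P runs from .012 to .026. With unrestricted rounding it runs from .003 to .080.
- No other two-arm comparison that can be recomputed from the tables reaches .05; the next lowest is stepping, at about .11. Weight gives .27 and BMI .46.

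**3. How surprising is this?** Taking 26 as a low count of baseline variables and treating them as independent, the chance of two or more P values below .05 is 1 − .95²⁶ − 26×.05×.95²⁵ = 1 − .264 − .361 = .38. Counting every printed P value (14 + 12 + 8 = 34 in Tables 1, 2 and 3), it is 1 − .175 − .313 = .51.

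**4. Arms as randomised.** The article does not say to which arm the two top-band dropouts belonged, so all cases are shown:

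| Top-band dropouts from control | Control | Exercise | Fisher P |
|---|---|---|---|
| 0 | 2/22 (9%) | 12/23 (52%) | .003 |
| 1 | 3/22 (14%) | 11/23 (48%) | .023 |
| 2 | 4/22 (18%) | 10/23 (43%) | .11 |

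Using all three bands and every allocation of the ten dropouts that fits the 7/3 split, the chi-square P runs from .002 to .19. If income among dropouts were unrelated to arm, the last row of the table would have probability 7/10 × 6/9 = .47.

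**The case against.** The strongest reply is that nothing is hidden. The body text names the three groups, the tables head three columns, the dropout split is given, and the income counts and heights by completer group are in plain view. That is correct. It is why this is a reporting error, mainly in the Abstract, and not a concealed comparison.

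A second reply is that two unadjusted P values picked from a long list prove little. This also stands: step 3 shows that such a result is unremarkable. The point therefore rests on the size of the income gap and on a sentence that is untrue by its own .05 criterion, not on significance. Height is secondary, since its printed .05 already alerts a reader and weight and BMI do not differ between the arms.

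Third, the planned analysis compares change between arms, so stable baseline differences largely cancel. Income would have to affect change over the 12 weeks, and the article gives no evidence that it does. The Introduction's remark on environment and lifestyle is also made in the context of differences between black and white women, so it supports interest in socioeconomic status only in general terms.

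A reader might infer that randomisation failed, or that dropout either created the gap or can be ruled out as its cause. The documents support none of these. Chance is an adequate explanation, and the as-randomised result ranges from clear to inconclusive depending on an allocation that is not reported.

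**Conclusion.** The no-difference statement is wrong as written for the two groups the Abstract names. No exercise-versus-control test is reported, and the article's own counts show a 37-point gap in the top income band between the analysed arms, with a height difference of about 5 cm. In the arms as randomised a top-band gap of at least 25 points remains (18% against 43%), but dropout's share in the completers' larger gap is unknown.

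The income figures rest on the Table 1 counts as printed. The height P rests on means and SDs rounded to 1 cm. It would go too far to conclude that the primary between-arm contrast is biased. What follows is that readers are given an assurance of balance that the data do not bear out, in an article whose stated purpose is to identify causal pathways.

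**What to change.** - Present Tables 1 to 3 by randomised arm (control 22, exercise 23), with completers and dropouts shown within each arm.
- Replace the no-difference sentences in the Abstract and in the baseline section with a description of the income and height differences by counts and size, not by P value.
- Keep the planned primary analysis. A model of the primary contrast adjusted for the three-level income band is optional. If run, label it a post hoc sensitivity analysis, because the covariate would be chosen after its imbalance was seen.

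The cost is reworking three tables and a few sentences from data already held, and acknowledging an imbalance in print. The optional model would spend 2 degrees of freedom with 35 women.

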**Conclusions:**

The study describes a research protocol for an exercise intervention to understand the mechanisms underlying insulin sensitivity and secretion in obese black SA women and aims to identify causal pathways underlying the high prevalence of insulin resistance and risk for T2D in black SA women, targeting specific areas for therapeutic intervention.

**Trial Registration:**

Pan African Clinical Trial Registry PACTR201711002789113; http://www.pactr.org/ATMWeb/ appmanager/atm/atmregistry?_nfpb=true&_pageLabel=portals_app_atmregistry_portal_page_13 (Archived by WebCite at http://www.webcitation.org/6xLEFqKr0)

## Introduction

### Background

Type 2 diabetes (T2D) is a significant contributor to morbidity and mortality worldwide [1]. Globally, sub-Saharan Africa has the highest projected rate of increase in T2D over the next 25 years, increasing by 2.5-fold from 14.2 million in 2015 to 34.2 million by 2040 [1]. T2D and its associated morbidity and mortality rates are more prevalent in populations of black African origin than white populations [2-4]. Within South Africa (SA), the prevalence of T2D has increased significantly over the past 20 years, particularly in black African urban-dwelling populations [5]. Higher prevalence rates in SA are found in women (14.7%) compared with men (11.3%) [5]. This high T2D rate is compounded by the high prevalence of obesity and insulin resistance in black women [6-8]. Insulin resistance in black populations is associated with hyperinsulinemia, as a result of greater insulin secretion and reduced hepatic insulin clearance [7-9]. However, with increasing age, insulin secretion in relation to insulin sensitivity decreases in black women and is associated with impaired glucose tolerance and T2D [10].

The pathogenesis of insulin resistance in black women is complex and differs from that in their white counterparts [11]. Despite greater insulin resistance, black women have less visceral adipose tissue (VAT) but more peripheral (gluteal-femoral) subcutaneous adipose tissue (SAT) deposition [12-14]. This paradox may be explained, in part, by differences in adipose tissue biology [11]. Compared with white women, SAT of black women is hypertrophic, has a reduced adipogenic capacity [15], a higher inflammatory profile [16], less vascularization, and increased fibrosis [17]. These findings are suggestive of pathological adipose tissue expansion, which is typically associated with ectopic fat deposition and insulin resistance [18]. However, we found that obese black women accumulated less hepatic fat than their white counterparts [19], which corresponds with their lower VAT levels [12], but had similar intra- and intermyocellular lipid content of the soleus muscle [19]. Furthermore, the association between ectopic fat and insulin sensitivity was more robust in black as compared with white women [19]. These distinct obesity-related phenotypic differences may differentially impact the risk for insulin resistance and T2D in black and white women. However, these studies were cross-sectional and provide little insights into the causal pathways involved.

Exercise training, via its effects on multiple organs and systems, reduces insulin resistance and the risk of T2D (for reviews [20-22]). Recent studies have suggested an important crosstalk between skeletal muscle, liver, adipose tissue and the pancreas [23-25], which is altered in response to exercise training [23]. The effects of exercise training on insulin sensitivity are primarily through insulin action in skeletal muscle [26], which involves many mechanisms, including changes in the insulin signaling, inflammation, reactive oxygen species (ROS), metabolic flexibility, mitochondrial biogenesis, and ectopic fat accumulation. Within adipose tissue, exercise training decreases the obesity-induced dysregulated expression of adipokines, adipocyte size, ROS and inflammation, and increases vasculature [27]. In addition, the importance of the gastrointestinal microbiome for diabetes risk has recently been recognized [28] and is responsive to exercise [29,30]. Indeed, advances in omics technologies have improved our understanding of systems biology in diseased states and can be used to identify novel pathways underlying insulin resistance and T2D risk.

Although, we can identify biological and physiological correlates of insulin resistance in black women, these may merely reflect adaptations to environmental and lifestyle factors. There are marked ethnic differences in socioeconomic status, dietary intake, and physical activity between black and white SA women [12]. In terms of physical activity, black women accumulate activity through walking for transport (typically performed at a low intensity), while participation in leisure activities that are generally performed at moderate-to-high intensities is uncommon [12,31]. Accordingly, black women have very low cardiorespiratory fitness levels, which associates with their high levels of obesity and insulin resistance [32].

Overall, exercise training improves cardiorespiratory fitness and reduces cardiometabolic risk factors associated with the development of T2D. Accordingly, exercise training is consistently used as a model to examine putative mechanisms underlying insulin resistance and risk for T2D. To our knowledge, there are no studies that have examined the effect of exercise training on insulin resistance in obese black SA women who are at high risk for T2D. Therefore, the primary purpose of this research study is to gain a better understanding of the causal mechanisms underlying insulin resistance and risk for T2D in black SA women, using exercise as an intervention.

### Aims and Objectives

The aim of the study was to identify mechanisms underlying the changes in insulin sensitivity and secretion in response to a 12-week aerobic exercise intervention in obese black SA women.

The objectives of the study were as follows:

to measure changes in insulin sensitivity and secretion (primary outcomes) in response to the 12-week intervention compared with the nonexercise control groupto measure changes in potential primary and secondary determinants (secondary outcomes) of insulin sensitivity and secretionto examine the associations between changes in insulin sensitivity and secretion and changes in the primary and secondary determinants

Primary determinants were as follows:

cardiorespiratory fitnessbody composition and body fat distributionblood pressurelipid profile, including high-density lipoprotein (HDL)- and low-density lipoprotein (LDL)-cholesterol subclasses and HDL functionalityectopic fat deposition (skeletal muscle, liver, and pancreas)skeletal muscle expression of genes and proteins involved in insulin signaling, oxidative capacity, and mitochondrial biogenesisskeletal muscle and serum metabolomics and lipidomic profilegluteal and abdominal subcutaneous adipose tissue expression of genes and proteins involved in inflammation, insulin signaling, oxidative stress, vascularization, adipogenesis, and lipid metabolismcirculating inflammatory cytokine, myokine, and adipokine concentrationsskeletal muscle and adipose tissue mitochondrial respiration and hydrogen peroxide production;gastrointestinal microbiota

Secondary determinants were as follows:

energy expenditure and substrate metabolism at rest and during exercisehabitual physical activity and sedentary behavior patternsdietary intake, red blood cell, and adipose tissue fatty acid compositionsleep quantity and qualitypsychological well-beingperceptions of body image, healthy behaviors, and the exercise intervention

## Methods

### Study Design

In this randomized controlled research study, 45 obese sedentary black SA women were block (2-4 participants) randomized (Microsoft Office, Excel, 2013) into control or experimental (exercise) groups (Figure 1). Block randomization was performed by the project manager after participants completed preintervention testing to ensure that investigators performing the testing were blinded to group allocation. The exercise group completed 12 weeks of supervised combined aerobic and resistance training (40-60 min, 4 days/week) but maintained their usual dietary behaviors. The control group were instructed to continue their habitual physical activity and dietary behaviors and to refrain from initiating any exercise programs. Before and following the 12-week intervention period (exercise or control), insulin sensitivity and secretion (primary outcome), as well as the proposed determinants of insulin sensitivity and secretion (secondary outcomes) were measured. In addition, dietary intake, sleep quality and quantity, physical activity, and sedentary behavior were monitored for a minimum of 4 days every 4 weeks.

This study was approved by the Human Research Ethics Committee at the University of Cape Town (HREC REF:054/2015). The study was performed in accordance with the principles of the Declaration of Helsinki (1964, amended last in Fortaleza Brazil, 2013), ICH Good Clinical Practice (GCP), and the laws of SA. Participants provided written informed consent before participation in the screening and the research study. Participant recruitment and testing procedures occurred over an 18-month period, between July 2015 and December 2016. Sample and data analysis began in January 2017 and are currently ongoing.

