### Overview of Testing Procedures

The study design and stepwise stages of the protocol are described in Figure 2. Before and following the 12-week intervention, participants completed 4 data collection sessions. At the first session, participants completed a cardiorespiratory fitness test of peak oxygen consumption (VO_2peak_), and body composition was measured by dual energy x-ray absorptiometry (DXA). At least 72 hours later, the participants spent a night at the laboratory where they were given a standardized evening meal at 8 PM and then required to fast overnight (10 hours). During the evening or early morning, participants were requested to provide a fecal sample. At 6 AM, the participants completed measures of resting metabolic rate (RMR) and substrate metabolism, and resting heart rate and blood pressure were measured. At 7 AM, fasting blood samples were collected and participants underwent a frequently sampled intravenous glucose tolerance test (FSIGT). During the FSIGT, the field worker administered the questionnaires, and the participants completed a 24-hour dietary recall and food frequency questionnaire with a Health Professions Council of South Africa registered dietician. The participants were then requested to complete a 3-day food diary. On a separate day, after a 10- to 12-hour overnight fast, participants completed steady-state exercise testing at 50% VO_2peak_. Thereafter, participants were provided a standardized meal and underwent a magnetic resonance imaging (MRI) scan. On the fourth day of data collection, and after 4 to 6 hours of fasting and 48 hours of rest, participants underwent skeletal muscle and abdominal and gluteal SAT biopsies. Accelerometers (ActiGraph and ActivPAL) were attached to the participants and worn for 7 days.

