#### Cardiorespiratory Fitness

To determine cardiorespiratory fitness, VO_2peak_ was measured using a treadmill-based (C, Quasar LE500CE, HP Cosmos, Nussdorf-Traunstein, Germany) graded exercise test. Participants were familiarized to the equipment before beginning the test, and heart rate was monitored throughout for the determination of HR_peak_ (Polar A300, Kempele, Finland). The initial 6 min of the test was designed based on a modified Bruce protocol to obtain three stages of steady state metabolism (see steady state protocol below) and the subsequent minutes were designed to obtain VO_2peak_ using a ramp protocol, adapted from Takagi et al [44]. Participants began at 3 km/hour at a 2% gradient for 2 min. The gradient increased by 2% for a further two 2-min segments. The following stages increased by 2% gradient every minute until 16%. Following this there was an alternate increase in speed (0.5 km/hour) and gradient (1%) until volitional exhaustion. This walking cardiorespiratory fitness test was designed for participants who were sedentary and are not familiar with gym-based equipment.

Pulmonary gas exchange was measured by determining O_2_ and CO_2_ concentrations and ventilation to calculate VO_2_ consumption using a metabolic gas analysis system (CPET, Cosmed, Rome Italy). Before each test, the gas meter was calibrated with a Hans Rudolph 3-liter syringe (Vacumed, Ventura, CA) and analyzers calibrated using standard gas mixtures of oxygen (26% O_2_ with the balance nitrogen) and carbon dioxide (4% CO_2_, 16% O_2_, and the balance nitrogen) (BOC Special Gas, Afrox Cape Town, South Africa). Ethanol burns for equipment calibration were conducted every 4 weeks (mean variance<2%).

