#### Fasting Blood Samples and Frequently Sampled Intravenous Glucose Tolerance Test (FSIGT)

Following the RMR measures, fasting blood samples were drawn, and an FSIGT was performed. A cannula was inserted into a vein of each arm. One arm was used for intravenous glucose and insulin infusions, and the other arm was heated and used for blood sampling. Fasting blood samples were drawn for the determination of adipokines, myokines, inflammatory markers and cytokines, lipid profiles and HDL- and LDL-cholesterol subtypes and HDL functionality, and red blood cell fatty acid composition, metabolomic and lipidomic analysis.

For the FSIGT, further 2 baseline samples were collected at −5 and −1 min before a bolus of glucose (50% dextrose; 11.4 g/m^2^ body surface area) was infused intravenously over 60 seconds beginning at time 0. At 20 min, human insulin (0.02 U/kg; NovoRapid, Novo Nordisk) was infused over 5 min at a constant rate (HK400 Hawkmed Syringe Pump, Shenzhen Hawk Medical Instrument Co., Shenzhen, China). Samples for determination of plasma glucose and serum insulin and c-peptide concentrations were drawn at 2, 3, 4, 5, 6, 8, 10, 12, 14, 16, 19, 22, 23, 24, 25, 27, 30, 35, 40, 50, 60, 70, 80, 90, 100, 120, 140, 160, 180, 200, 220, and 240 min.

Fasting blood samples were collected into EDTA, lithium heparin, fluoride oxalate, and SST tubes. Samples in SST tubes clotted for 30 min at room temperature, while the remaining samples were placed on ice before centrifugation. Samples were centrifuged at 3000 rpm for 10 min at 4°C. Plasma for glucose analysis was stored at −20°C, while the remaining serum and plasma was stored at −80°C. Red blood cells collected from EDTA tubes were washed by 2 cycles of sequential centrifugation at 1000 rpm and a final cycle of centrifugation at 3000 rpm for 10 min. Between cycles, saline (0.9% NaCl in distilled water) was used for resuspension and washing. Red blood cells were then stored at −80°C until the analysis.

Glucose and insulin concentrations from the FSIGT will be used to calculate the insulin sensitivity index (S_I_) using Bergman’s minimal model of glucose kinetics [49]. Glucose and c-peptide data will also be used in a two-compartment minimal model of C-peptide secretion and kinetics to calculate insulin secretion rate (ISR) using WinSAAM (version 3.3.0). ISR will then be used in a one-compartment insulin minimal model to determine insulin hepatic extraction index [50].

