#### Comprehensive Metabolite Profiling of the Serum and Muscle Metabolome

For the metabolite analyses, a combined platform of liquid (LC-QTOF-MS) and gas (GCTOF-MS lipids) chromatography coupled to mass spectrometry, in both positive and negative ionization modes will be used. This approach will enable a comprehensive coverage of serum and muscle metabolites with different chemical properties. All sample preparation and analyses will be performed according to a run order design to circumvent methodological biases that may interfere with results interpretation [64]. For example, samples from the same individual are prepared and analyzed in close connection while keeping the internal sample order randomized. Analytical batches will be balanced in terms of treatment group and quality control (QC) samples (ie, pooled from all samples) will be analyzed continuously.

Serum samples will be prepared according to A et al [65], using a 90/10, v/v methanol:water extraction including internal standards for metabolomics; and a 70/30, v/v chloroform:methanol extraction for lipidomics [66].

On an average, we will detect 2000 to 3000 peaks or more, and annotation/identifications will be done via the use of publically available library, in combination with *in house* library at the Swedish Metabolomics Centre (SMC). For targeted analyses and validation of findings, we will use triple quadrupole mass spectrometry techniques, such as LC-QqQ-MSMS or GC-QqQ-MSMS together with LC-TQMSMS and GC-TQMSMS in MRM-mode. Absolute quantification of specific compounds will be achieved by using calibration curves calculated from stable isotope labeled internal standards.

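### Randomising after baseline testing can blind only the pre-test, so it cannot support a claim of blinded outcome assessment

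*Protocol article*

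**What the plan says.** Study Design states that the project manager did the block randomisation "after participants completed preintervention testing to ensure that investigators performing the testing were blinded to group allocation". No other sentence in the article concerns blinding.

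Overview of Testing Procedures gives the timing of measurement: "Before and following the 12-week intervention, participants completed 4 data collection sessions". Aims and Objectives defines the primary outcomes as changes in insulin sensitivity and secretion compared with the control group, and the secondary outcomes as changes in their determinants.

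On the measures themselves:
- The fitness test in Cardiorespiratory Fitness finishes with an "alternate increase in speed (0.5 km/hour) and gradient (1%) until volitional exhaustion".
- In the section on the intravenous glucose tolerance test (FSIGT), the primary outcomes have still to be derived: "Glucose and insulin concentrations from the FSIGT will be used to calculate the insulin sensitivity index", and "Glucose and c-peptide data will also be used in a two-compartment minimal model of C-peptide secretion and kinetics".
- For metabolomics, "Analytical batches will be balanced in terms of treatment group".

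**The concern.** The sentence gives the timing of randomisation as the means of ensuring that testers were blinded. That timing protects one of the two measurements in each change score. A reader who takes the sentence to cover testing in general would credit the trial with blinded outcome assessment, which this device cannot provide.

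What is at stake is a difference between arms that comes from measurement. If the pre-test is blind and the post-test is not, any effect of a tester's or analyst's expectation falls on one side of the change and is not subtracted out. Exposure differs by measure. A walking test that ends at the participant's own limit is open to encouragement, and fitting a kinetic model or reading a blot can involve operator judgement. Glucose and insulin assays are much less exposed.

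**Working it through.** **Order of events.** The sequence in Study Design and Overview of Testing Procedures is:
1. Pre-test, four sessions. No allocation exists, so testers are blind whatever else is done.
2. Randomisation.
3. Twelve weeks of supervised exercise, or control.
4. Post-test, four sessions. Allocation exists, and the timing of step 2 hides nothing here.
5. Laboratory work, image processing and modelling, begun in January 2017 after testing had ended and described as ongoing. Again the timing of step 2 hides nothing.

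For an outcome defined as change = post − pre, the stated device covers the second term only.

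**What can still be masked.** The article's verb tenses separate pending work from completed work.
- Future tense: modelling of the insulin sensitivity index (S_I), insulin secretion and hepatic extraction; adipose RT-PCR; ELISA and Western blots; metabolomics and lipidomics; fecal sequencing.
- Past tense: MRI post-processing and MRS quantification, accelerometer analysis, and the glucose, insulin, C-peptide, lipid and inflammatory-marker assays.

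Both primary outcomes are therefore in the group where masking is still possible.

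**Illustration of size (bias values are assumptions; the document gives none).** With two time points, the planned repeated-measures ANOVA comparison of change between arms is equivalent to a t test on the change scores. With 20 exercise and 15 control completers there are 33 degrees of freedom. For a differential post-test bias of b SDs of the change and no true effect, the noncentrality is b / sqrt(1/20 + 1/15) = b / 0.342.

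| Assumed b | Noncentrality | Two-sided 5% test rejects |
|---|---|---|
| 0.1 | 0.29 | 5.9% |
| 0.2 | 0.59 | 8.8% |
| 0.3 | 0.88 | 13.7% |
| 0.5 | 1.46 | 29.5% |

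For VO2peak, Table 2 gives baseline SDs of 2.4 (exercise, n=20) and 3.0 (control, n=15) mL/kg/min. Pooled SD = sqrt((19 × 2.4² + 14 × 3.0²) / 33) = sqrt(235.44 / 33) = 2.67. An assumed effort difference of 0.5, 1 or 2 mL/kg/min is then 0.5/2.67 = 0.19, 1/2.67 = 0.37 or 2/2.67 = 0.75 baseline SD. The SD of change is not given, so these values cannot be entered in the table above. For S_I and secretion the document offers no basis for a figure.

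**The case against.** The strongest reply is that the sentence is true as written. Preintervention testing is named just before, so the testing can be read as the pre-test alone. That reading is fair. On it the sentence is accurate, but it then says nothing about the post-test half of any outcome, and a qualifier is still needed to stop the broader reading.

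Second, a condensed article may leave post-test masking to the full protocol. This also stands. A reader might infer that post-testers knew the arm, but no passage says so, and none says that the exercise facilitator did any testing. The point concerns what the stated device can achieve and does not depend on a missing detail.

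Three other inferences go too far:
- Balancing metabolomics batches by arm does not show that analysts know the arm. It guards against batch effects and can be done by someone who holds the key.
- Imaging, accelerometer and biochemical work is reported as done, so it cannot be treated as pending. The accelerometer validity rule also requires an exercise day in the exercise group only, so those files could not be fully masked to arm.
- The Discussion says only that improved insulin sensitivity is anticipated. That shows an expectation and does not show that it entered the data.

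The primary outcomes are also fairly well protected by fixed sampling times, largely instrument-based assays and named kinetic models. For VO2peak, participants cannot be blinded, so their own effort could differ by arm even with masked testers. Of the two post-test steady-state tests, only the second uses the post-intervention VO2peak; the first repeats the pre-intervention workload.

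**Conclusion.** The point holds in a limited form. Randomising after the pre-test blinds the pre-test. It does not blind the four post-test sessions or later processing, and so cannot support a claim of blinded outcome assessment. This follows from the order of events and needs no numerical assumption.

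The document does not establish that bias occurred, or how large it might be. The false-positive rates and the VO2peak shifts are illustrations from assumed bias values, and the VO2peak shifts are scaled to baseline SD although the outcome is a change. They show that a modest differential bias would matter with 35 completers; they do not measure one. The correction is worth making because the modelling of both primary outcomes was still to be done and masking it is cheap.

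**What to change.** 1. In Study Design, limit the statement to pre-intervention testing.
2. Run the work still in the future tense on codes that hide both arm and visit: S_I, insulin secretion and hepatic-extraction modelling, adipose RT-PCR, ELISA and Western blots, and metabolomics. The fecal sequencing can take the same codes. An existing team member who holds the key can keep the batches balanced by arm.
3. For VO2peak, report peak RER and peak heart rate by arm and visit, from the gas-exchange and heart-rate data already recorded, as a descriptive check of effort. Do not restrict the fitness comparison to tests that reach a peak-RER threshold: that would select on a post-randomisation variable among only 35 completers and could itself bias the contrast.
4. Completed MRI/MRS, accelerometer and biochemical work need not be repeated.

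The cost is a little relabelling of files and samples and one descriptive table. No new staff or procedures are needed.
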